## Background

1

Cerebral palsy (CP) is a permanent, non-progressive disorder caused by brain disturbances during fetal or infant development, affecting 1.5 to 3 out of every 1000 live births [1,2]. Symptoms vary widely, impacting functioning, body structures, activities, and societal participation, leading to disability. While CP is non-progressive, symptoms can evolve as individuals grow and societal expectations change. Multimorbidity is common among aging individuals with CP [3] possibly attributed to higher levels of sedentariness compared to peers [4], and a risk of decline in gross motor ability during adolescence [5]. This period may present an opportunity to intervene and prevent functional decline and health issues in adulthood.

Neuro(re-)habilitation utilizes the nervous system's inherent plasticity, promoting learning and adaptation through active participation, intensive training, task progression, goal setting, and motivation [[6], [7], [8]]. Improving and maintaining functional ability usually requires ongoing therapeutic engagement. However, limited resources often restrict access to supervised programs, particularly at high intensity. The necessity of traveling to a gym or clinic can further hinder attendance [9]. Home-based training shifts the emphasis from therapist-led sessions to self-initiated motor training. Evidence supports the feasibility and effectiveness of home-based training programs for infants and young children with CP, promoting integration into standard care [[10], [11], [12]]. These programs can improve balance [13], upper limb function, and parent satisfaction [14]. Significant improvements in upper limb skills were observed after eight weeks [14], while video-game-based training led to improvements across various functional tests after 20 weeks [15] with a reported average of 40 h of additional training. Compliance with home-based programs varies with self-reported adherence ranging from 56 % to 99 %. Recent findings suggest that extrinsic feedback from equipment or a coach enhances recovery and motor learning in stroke rehabilitation [16]. It's unclear if the effect arises from extrinsic feedback or is linked to higher intensity and adherence to training programs.

In the THRIVE-CP trial, we propose using the TIA app (Translating Intentions into Actions) and wearable Inertial Measurement Units (IMUs) for home-based motor training. The technology provides real-time performance feedback through music while objectively measuring attendance and adherence. Music Motion Feedback presents a potentially effective method to enhance meaningful changes in real-world movement behavior and functional improvement.

### Objectives

1.1

The THRIVE-CP trial evaluates the effectiveness of incorporating Music Motion Feedback into home-based motor training for adolescents and young adults with CP compared to home-based motor training without Music Motion Feedback. We hypothesize that the Music Motion Feedback group will demonstrate greater improvements in real-world movement behavior, functional improvement, limb function, and perceived goal performance than the control group. Additionally, we expect the Music Motion Feedback group to attend and adhere more to the training program.

## Methods

2

This protocol is reported according to the Standard Protocol Items: Recommendations for Interventional Trials (SPIRIT statement) [17].

### Trial design

2.1

This is a two-arm parallel assignment randomized clinical superiority trial in which adolescents and young adults with CP self-administer home-based motor training with or without Music Motion Feedback. Outcomes will be assessed before randomization, after 12 weeks of intervention (end of intervention - T2), and to evaluate the sustainability of potential improvements after 24 weeks (follow-up - T3). The trial design is visually presented in Fig. 1.

**Fig. 1 fig1:**
[figure not shown]
The THRIVE-CP trial design **Note:** Inertial Measurement Unit (IMU). Individualized motor training programs, tailored to individual goals, are created by [name] before randomization. These programs focus on three core components: 1) task specificity, 2) training intensity, and 3) virtual conferences. [name] hosts virtual conferences biweekly with each participant during the training period to improve adherence and adjust the program to optimize training intensity. A third-party allocator will visit participants after randomization, where the controls will receive a code that unlocks the TIA app on a tablet with the message “You are now ready for training.” In contrast, the Music Motion group participants will receive a code granting access to the Music Motion Feedback feature in the TIA app. Participants in both groups will engage in self-administered, home-based training for 12 weeks while wearing an IMU on the targeted extremity during training. Attendance and adherence data will be collected on the tablet for both groups, though not accessible to participants.

### Setting, trial site, and recruitment

2.2

Participants will be recruited consecutively from the CP Youth Clinic at Copenhagen University Hospital — Rigshospitalet, Denmark. The clinic's nurse and physical therapist will invite eligible individuals to participate during routine consultations (i.e., when individuals are 15, 17, and 21 years old). Individuals who have previously attended the CP Youth Clinic and consented to research invitations will be invited to participate.

### Eligibility criteria

2.3

Individuals with CP aged 15 to 25 at enrollment are eligible to participate if they have sensorimotor deficits in at least one limb and are classified within GMFCS-E&R levels I-V. They must show motivation to develop new motor skills or recover lost ones, as indicated by their or their proxy's ability to express a specific goal they wish to achieve. They must be able to follow instructions independently or with caregiver support and be capable of providing informed consent to participate. Individuals will be excluded from participation if they have dyskinetic CP, significant health risks, have undergone major orthopedic or neurosurgical procedures within six months preceding enrollment or planned during the intervention period, or minor procedures that could temporarily affect training or movement behavior within one month before enrollment or during the trial. Eligibility for borderline cases is determined by the principal investigator in consultation with the treating physician. Botulinum neurotoxin type A (BoNT-A)-naïve individuals will be excluded if they have received intramuscular injections within three months before baseline. Individuals undergoing routine BoNT-A injections are eligible, and injections in muscles not directly targeted by the training program do not preclude participation.

### Individualized motor training programs

2.4

Participants in both groups will engage in home-based motor training grounded in principles of neural plasticity [[6], [7], [8]]. After informed consent, an experienced physical therapist ([name]) will develop an individualized motor training program with each participant. The process includes setting a long-term goal using the Canadian Occupational Performance Measure (described under tertiary outcomes), conducting neurological, biomechanical, and motor control assessments to identify specific movement limitations, and focusing on key factors for goal achievement. Short-term goals will be established following the SMART framework [18]. Participants will wear a small wireless IMU (MetaMotions from Mbientlab, San Francisco, United States) on the targeted body part during training (e.g., on the thigh for sit-to-stand), which will transmit movement signals via Bluetooth to a tablet's TIA app. IMU and tablet will be provided.

**Task-specific training** emphasizes meaningful, everyday activities, emphasizing neural plasticity's dependence on experience. Addressing each participant's unique challenges and goals is essential. Programs will foster intentional, active practice and minimize reliance on verbal or physical assistance, using visual cues to guide movement.

**Intensity** emphasizes high effort and challenging training to induce neuroplastic changes. It will be approached as a dynamic interplay between frequency, repetition, difficulty, resistance, session duration, and overall program length, recognizing that optimal learning occurs under conditions that do not yield peak performance [19]. The training setups will allow participants to perform independently and at their convenience throughout the day.

**Virtual conferences** will be conducted by licensed physical therapists trained in the THRIVE-CP protocol. Five sessions of approximately 30 min each will promote adherence to the program and optimize training intensity. Participants' skill acquisition, training tolerance, and short-term goals will be reviewed to either advance progression or address regression while maintaining a balance between task difficulty and performance.

### Music Motion feedback

2.5

The Music Motion Feedback group will use a specific code to access the feedback feature in the TIA app for their motor training program. This app provides real-time auditory feedback to inform participants if they fail to meet the required intensity during practice.

TIA converts signals (from accelerometers and gyroscopes) gathered from IMUs worn on targeted body parts into commands. Originally designed for users with movement disorders to control devices like music volume and lights, the app has been adapted to support a rehabilitative approach, where music becomes distorted if the participant does not meet the training intensity threshold.

Before each session, the TIA app guides participants through a process to set their intensity thresholds. This involves participants moving as quickly and precisely as possible through the training movements while utilizing their full range of motion. Each participant will have an individual percentage threshold in their training program based on factors such as prescribed training frequency, repetitions, difficulty, resistance, session duration, and the overall length of the program. During training, each complete cycle of movement that reaches the intensity threshold (as a percentage of the current maximum) will trigger specific musical elements like a drumbeat or vocals in the participant's chosen music. If the participant fails to meet the threshold, elements of the music will drop out, providing error-related auditory feedback to encourage correction.

### Randomization

2.6

Participants will be assigned to groups using matched pairs randomization with a 1:1 allocation ratio. Matching will be based on dichotomized ages (adolescents 15–19 years, young adults 20–25 years) and GMFCS-E&R classifications. Within each stratum, participants will be grouped into pairs. A computer-generated randomization sequence will assign the first participant in each pair to either group, with the second assigned to the alternate. [name] will enroll participants and extract age and GMFCS-E&R classifications to create pairs. A third-party allocator will conduct randomization to ensure allocation concealment, with the sequence securely stored and revealed only after statistical analysis is complete.

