### Blinding

2.7

Outcome assessors, the physical therapist responsible for developing the motor training programs and conducting virtual conferences ([name]), participants, and the statistician will be blinded to group allocation. To minimize expectation bias participants will not be informed that only one group will receive Music Motion Feedback during training. Participants will be instructed not to discuss or disclose their allocation with outcome evaluators. Virtual conferences will focus exclusively on motor training programs and goals, deliberately omitting any reference to intervention features like Music Motion Feedback.

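### Pairing makes the second member's arm certain once the first's is known; the enroller forms the pairs, and the non-disclosure instruction names only outcome evaluators

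*Protocol article*

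**What the plan says.** Section 2.6 (Randomization) sets the method: "Participants will be assigned to groups using matched pairs randomization with a 1:1 allocation ratio". The matching factors are two age bands and GMFCS-E&R: "Matching will be based on dichotomized ages (adolescents 15–19 years, young adults 20–25 years) and GMFCS-E&R classifications". Eligibility (section 2.3) admits people "classified within GMFCS-E&R levels I-V", so there are up to 2 × 5 = 10 strata. The rule inside a pair is: "A computer-generated randomization sequence will assign the first participant in each pair to either group, with the second assigned to the alternate". One role, with the name removed, "will enroll participants and extract age and GMFCS-E&R classifications to create pairs". The safeguard is a third party: "A third-party allocator will conduct randomization to ensure allocation concealment, with the sequence securely stored and revealed only after statistical analysis is complete".

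Section 2.7 (Blinding) lists outcome assessors, the therapist who develops programs and holds the virtual conferences, participants and the statistician as blinded. Its instruction to participants reads: "Participants will be instructed not to discuss or disclose their allocation with outcome evaluators". The same section says that participants are not told that only one group gets the feedback, and that conferences leave out any mention of it.

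The order of events is given in the note to Fig. 1: "Individualized motor training programs, tailored to individual goals, are created by [name] before randomization". Section 2.4 gives five conferences of about 30 minutes per participant. Section 2.5 describes the feedback as elements of the participant's chosen music dropping out when the threshold is missed.

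**The concern.** A third-party allocator conceals a list. It cannot conceal an allocation that follows by rule from one already known. Under the pair rule, whoever learns the first member's arm and knows the pairing knows the second member's arm without seeing the list.

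The text leaves a route by which this could happen. The participant can hear which version of the app they have. Section 2.7 gives program writing and conferences to one therapist role, so the person who writes a later participant's program may already be talking regularly with that participant's pair partner. Participants are asked to keep quiet towards outcome evaluators, but no such request covers this therapist or the enrolling staff.

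What is decided before randomization bears directly on the results. The goal and program fix the targeted limb, on which the primary outcome is measured (section 2.10.1). They decide whether the upper- or lower-limb secondary outcomes apply (section 2.10.2). They also set the prescribed dose, which is the denominator of the attendance and adherence categories (section 2.13.3.2). Foreknowledge at that stage could make these choices differ by arm. Knowledge gained later would still unblind the therapist to the partner while that partner's program is being adjusted.

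**Working it through.** **Plan's own figure.** The article gives no figure for predictability. Its only related figure is power: 81.8 % with 58 participants and a standardized difference of 0.76 (section 2.13.2). With 29 per group and two-sided 5 % (assumed, in line with the 95 % interval), the normal approximation is Φ(0.76 × √(29/2) − 1.96) = Φ(2.894 − 1.960) = 82.5 %. The noncentral t gives 81.2 %. The stated figure is reproduced closely, and nothing below changes it.

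**1. Allocations fixed by the partner's arm.**
- All pairs complete: 70 / 2 = 35 of 70 = 50 %.
- Lower limit, with all 10 strata ending on an odd number: (70 − 10) / 2 = 30 of 70 = 43 %.
- Expected value. The Discussion projects 70 % at levels I–II. Assumed here: 35 % at each of I and II, 10 % at each of III, IV and V, and 50–70 % adolescents. For a stratum with share p, the chance of an odd count is [1 − (1 − 2p)^70] / 2, which is close to 0.5 in every stratum. About 5 participants are therefore unpaired, and (70 − 5) / 2 = 32.5 of 70 = 46 %.

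**2. How often the next arm can be guessed.** Let q be the share of first members whose arm leaks, with all pairs complete. The correct-guess rate is 0.5 + 0.25q.

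| q | correct guesses |
|---|---|
| 0 | 50 % |
| 10 % | 52.5 % |
| 25 % | 56.25 % |
| 50 % | 62.5 % |
| 100 % | 75 % |

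With 32.5 fixed allocations and q = 100 %, the rate is (32.5 + 0.5 × 37.5) / 70 = 73 %.

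**3. Comparison with undisclosed blocks of 2 and 4**, equally likely, all earlier arms in the stratum known (exact enumeration).
- Position 2: the best guess is the opposite arm, correct with probability ½ × 1 + ½ × ⅔ = 83.3 %. It is never certain.
- Position 3: certain only if the first two arms agree, which needs a block of 4: ½ × ⅓ = 1/6. Best guess: 1/6 + 5/6 × ½ = 58.3 %.
- First six positions, certain: 0, 0, 1/6, 1/6, 1/12, 1/12. Mean 8.3 %.
- First six positions, best guess: 50, 83.3, 58.3, 91.7, 54.2, 87.5 %. Mean 70.8 %.

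| Participants in stratum | certain, mixed 2/4 | best guess, mixed 2/4 | certain, pairs | best guess, pairs |
|---|---|---|---|---|
| 6 | 8.3 % | 70.8 % | 50 % | 75 % |
| 8 | 9.4 % | 71.4 % | 50 % | 75 % |
| 14 | 10.0 % | 71.7 % | 50 % | 75 % |

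Mixed blocks remove most of the certainty, but little of the guessing advantage. Step 2 shows that the leak rate matters more than the block size.

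**4. Timing.** Section 2.2 has consecutive recruitment at one clinic, and section 2.6 speaks of a first and a second participant. Section 2.10 puts baseline within a week before the intervention starts. Randomizing both members together would need two people from the same stratum to reach baseline at nearly the same time. Sequential assignment is the likelier reading, but section 2.6 does not state it.

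**The case against.** The strongest reply is that section 2.7 already addresses the conference channel: the therapist is to be blinded, conferences keep to programs and goals, and participants do not know that the arms differ in the feedback. This stands in part. It governs what the therapist raises. It does not govern what a participant volunteers, and someone unaware that music distinguishes the arms has little reason to hold it back.

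Second, names are removed, so the documents do not show that the enroller is the conference therapist, and section 2.4 speaks of therapists in the plural. This stands for the enroller. Section 2.7 nevertheless describes program writing and conferences as one role.

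Third, section 2.6 could mean that pairs are formed before either member is randomized. Foreknowledge could then not affect the second member's enrollment, although one known arm would still reveal the other. Even under sequential assignment, conferences begin only after training has started, so a partner whose program is already written by then is affected only through unblinding.

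A reader might infer that half of all allocations will be known in advance, or that concealment has failed. The documents support neither. No leak is reported, and 50 % is a ceiling that applies only if every pair is complete and every first arm is known.

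**Conclusion.** The point holds as a conditional weakness that is cheap to reduce. Section 2.6 fixes a block of two and has the enroller form the pairs, and section 2.7 limits non-disclosure to outcome evaluators. Given a leak, up to 35 of 70 allocations are determined. Under the severity and age split assumed above the figure is about 32–33 (46 %), with limits of 30 and 35.

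Influence on the partner's enrollment, goal, limb and program further requires sequential assignment and a leak in time. Unblinding of the partner requires only the leak and knowledge of the pairing. The issue is selection bias and unblinding, not sample size. It would also be wrong to infer that changing the block size solves the problem: with full history known, the best-guess rate falls by only about 3–4 percentage points.

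**What to change.** 1. **Section 2.7:** extend the instruction not to disclose allocation to conference therapists and enrolling staff. One sentence, no practical cost. It acts on the leak itself.
2. **Section 2.6:** have the third-party allocator, not the enroller, form the pairs or hold the stratum position, and require goal, targeted limb and program to be recorded before the allocator is contacted. State whether the first member is randomized before the second is enrolled. This costs a change of task and a dated record. Its limit is that an enroller who knows age and GMFCS-E&R level could still count positions, so it supports change 1 and does not replace it.
3. **Section 2.6, secondary:** replace pairs by undisclosed, randomly mixed blocks of 2 and 4 in the same strata. This needs a new computer-generated list. The primary model in section 2.13.3.1 has no pair term, so it need not change. The downside is a within-stratum imbalance of up to 2 instead of 1, and more incomplete blocks at GMFCS III–V, where each stratum would hold about 2–5 participants under the assumed split (70 × 0.10 × 0.3 = 2.1 to 70 × 0.10 × 0.7 = 4.9).

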### Blinding

2.7

Outcome assessors, the physical therapist responsible for developing the motor training programs and conducting virtual conferences ([name]), participants, and the statistician will be blinded to group allocation. To minimize expectation bias participants will not be informed that only one group will receive Music Motion Feedback during training. Participants will be instructed not to discuss or disclose their allocation with outcome evaluators. Virtual conferences will focus exclusively on motor training programs and goals, deliberately omitting any reference to intervention features like Music Motion Feedback.

### Concomitant care and interventions

2.8

All participants should maintain their usual care routines. This care may include, but is not limited to, services provided by physical therapists, occupational therapists, speech therapists, and medical professionals in managing spasticity, pain, or seizures [1].

### Criteria for modifying or discontinuing interventions and participation

2.9

Changes to the motor training program may occur outside of the standard progression or regression, provided the goals are maintained. These occur during scheduled virtual conferences, either at the participants' request, in response to reported musculoskeletal issues, or due to safety concerns. If a participant requires surgery affecting functional ability and training during the trial, faces an illness that necessitates more than a week of hospitalization, or if Botox-naïve participants receive injections, their participation will be discontinued. If a participant withdraws from the trial, discontinues the motor training program, or is lost to follow-up, they will be asked whether the collected data can be used for analysis.

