#### Statistical methods

2.13.3

The distributions of continuous data will be assessed using Quantile-Quantile (Q-Q) plots, histograms, and the Shapiro-Wilk test. Normally distributed continuous data will be analyzed with parametric statistics. If normality is not met, a logarithmic transformation will be applied. Ordinal data will use non-parametric statistics. Categorical data will be presented as frequencies and percentages. An intention-to-treat analysis will include data from all trial participants.

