#### Missing data

2.13.4

To address dropouts and discontinuations, including participants who meet exclusion criteria during the trial, we will use multiple imputations to generate overall estimates and standard errors that account for the uncertainty associated with the imputation.

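### Three post-randomisation events end trial participation, so later outcomes are imputed under an intention-to-treat label even where they could have been observed

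*Protocol article*

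**What the plan says.** Section 2.9 (criteria for modifying or discontinuing interventions and participation) lists three triggers:

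- surgery: "If a participant requires surgery affecting functional ability and training during the trial"
- illness: "faces an illness that necessitates more than a week of hospitalization"
- injections: "or if Botox-naïve participants receive injections"

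The stated consequence is that "their participation will be discontinued".

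A separate sentence in the same section covers people who withdraw, stop the training programme or are lost to follow-up. Of all three groups it says that "they will be asked whether the collected data can be used for analysis".

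Section 2.13.4 (Missing data) reads: "To address dropouts and discontinuations, including participants who meet exclusion criteria during the trial, we will use multiple imputations". Section 2.13.3 (Statistical methods) states: "An intention-to-treat analysis will include data from all trial participants".

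Section 2.10 makes T2 (12 weeks) the primary endpoint, with T3 at 24 weeks. Nothing in the article provides for T2 or T3 assessment of a participant after one of the three events.

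**The concern.** An intention-to-treat comparison asks what happened to everyone randomised, whatever occurred afterwards. That requires collecting outcomes after such events where possible. Here the protocol ends participation, which stops collection, and fills the gap with imputed values. The participants stay in the denominator, but their contribution comes from a model. The article states no hypothetical estimand (the effect had the event not occurred) that would make this a deliberate choice.

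The data-use sentence raises a different problem. Stopping training is not withdrawal of consent, yet both lead to the same question. Section 1.1 hypothesises better attendance and adherence with feedback, so stopping may be more common in the control arm. If some of those who stop decline the use of their data, the loss could be related both to arm and to outcome. It could also thin the low attendance and adherence bands (below 33 % of the prescribed dose) that Section 2.13.3.2 compares between the arms.

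**Working it through.** **1. Does the wording end follow-up or only training?** The heading of Section 2.9 names interventions and participation as separate things, and the sentence on the three events uses the second. Section 2.13.4 is consistent with exit from the trial: it treats discontinuations as a source of missing data and expressly includes people who come to meet exclusion criteria. No other section restores their visits.

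**2. What is lost, by timing.**

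| Event | T2 (primary) | T3 |
|---|---|---|
| Before T2 | imputed | imputed |
| Between T2 and T3 | observed | imputed |

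**3. Could the outcome have been observed?** The primary outcome is 72 hours of sensor wear (Section 2.10.1), not a maximal-effort test, so at least some participants could probably provide it. The design already observes outcomes after injections in routine users (Section 2.3) and examines days since injection as a covariate (Section 2.13.5). That outcomes are obtainable is still an inference; some people will be unable or unwilling.

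**4. The plan's own figures.** Section 2.13.2 gives a standardised mean difference (SMD) of 0.76, 58 participants, 81.8 % power and 70 enrolled. Alpha is not given there; I take two-sided 0.05. With 29 per arm, power is 82.5 % by the normal approximation and 81.2 % by the two-sample t-test, so the stated figure reproduces closely. The dropout allowance is (70 − 58)/70 = 17.1 %. It covers dropouts in general and is not a rate for the three events.

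**5. Illustration of direction, with assumed inputs.** Suppose a share f of each arm is discontinued, imputation gives them the full SMD of 0.76, and their real effect is e. The SMD with everyone followed is (1 − f) × 0.76 + f × e.

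| f | e = 0 | Overstatement | e = 0.38 | Overstatement |
|---|---|---|---|---|
| 3 % | 0.737 | 0.023 | 0.749 | 0.011 |
| 6 % | 0.714 | 0.046 | 0.737 | 0.023 |
| 10 % | 0.684 | 0.076 | 0.722 | 0.038 |
| 17 % | 0.631 | 0.129 | 0.695 | 0.065 |

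The overstatement runs from about 0.01 to 0.13 SMD. Neither f, nor e, nor the imputation model is given in the article.

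**6. Would follow-up raise power?** Suppose 6 of the 12 allowed losses were observed, giving 64 participants (32 per arm). T-test power then depends on the effect in those six:

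- full effect: SMD 0.76, power 84.9 %
- half effect: (58 × 0.76 + 6 × 0.38)/64 = 0.724, power 81.4 %
- no effect: 58 × 0.76/64 = 0.689, power 77.4 %

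Against 81.2 % with 58, the change may go either way.

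**7. Selective non-use of data.** If the analysed values miss the true ones by the same gap in both arms, the shift is (difference in loss between arms) × gap. With assumed differences of 2 to 10 percentage points and gaps of 5 to 20 points of percentage change, it ranges from 0.02 × 5 = 0.1 to 0.10 × 20 = 2.0 points, against a margin of 10 %. The formula gives zero when loss is equal, so it does not measure the problem in step 5.

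**The case against.** The strongest reply is that the listed events are narrow. Only surgery that affects function and training, more than a week in hospital, or injections in people not previously treated lead to exit. Routine injections do not. An event after T2 leaves the primary endpoint intact, and some participants could not be assessed after such an event anyway. All of this stands and limits the number affected.

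A second reply is that the imputation model and further sensitivity analyses belong to the analysis plan, which is not shown. That is right as far as it goes: the article does not fix which values imputation would yield, so one cannot assert that these people are analysed as if the event had not occurred. But no analysis plan can recover visits that were never made. The data-collection rule is fixed in the protocol.

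A reader might also infer that people who stop training are removed. The text does not say so. They are asked about their data, and nothing bars them from T2 or T3. Nor does the article give any reason why the three events should differ by arm: the adherence argument applies to those who stop training, and there only to non-use of data.

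**Conclusion.** The point holds in limited form. Sections 2.9 and 2.13.4 together stop outcome collection after three post-randomisation events and substitute imputed values, which sits badly with the intention-to-treat statement in Section 2.13.3. The wording on data use for people who only stop training adds an avoidable route to selective loss.

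The size cannot be determined. The article gives no rate for the events, for stopping training or for refusal of data use, and no imputation model. The ranges in the working show scale under assumed inputs and are not estimates. A reader might infer a definite bias or a power gain from longer follow-up; the article supports neither. The conclusion rests on reading the end of participation as the end of assessments, which the section heading and the missing-data section both favour. It is a worthwhile, inexpensive improvement and not a fatal flaw.

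**What to change.** Keep the rules for stopping training exactly as they are, and separate them from follow-up:

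1. In Section 2.9, state that participants who meet a listed event or stop training are still invited to T2 and T3 where they are able and willing.
2. In Sections 2.13.3 and 2.13.4, state that their observed data enter the primary intention-to-treat analysis and that only values not obtained are imputed.
3. Ask about the use of collected data only when consent is withdrawn.

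The cost is a change of wording and a few additional assessments, of a kind already scheduled, among people already enrolled. Some will decline or be unable to attend, so imputation will still be needed for them. The change has to be made while the trial is running, since missed visits cannot be recovered at analysis.
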